### Study Procedures for Cross-Sectional Data Collections

The 2 data collection rounds required for achieving construct validity will be performed using an e-survey or paper form based on patients’ preferences. E-survey is a more accessible and practical approach to gathering data from the desired group using a web survey link. The paper form will be delivered to patients in OAC who will prefer this approach. Considering that some patients could be older, the paper form could overcome the possible challenges that they could have in using an e-survey approach. A preidentified health care professional will oversee patients’ enrollment, get informed consent, and perform data management and monitoring. Each obtained paper form or electronically collected data will be registered (or transferred in the case of data collected via SurveyMonkey [SurveyMonkey Inc]) in REDCap (Research Electronic Data Capture) software (Vanderbilt University; ie, electronic case-report forms). REDCap works as a web-based repository of the data collected. Both SurveyMonkey and REDCap are compliant with the European General Data Protection Regulation.

### Eligibility Criteria for Phase 2

Inclusion criteria for participation in the study are (1) the patients must be aged 18 years or older, (2) have a confirmed diagnosis of NVAF, (3) be outpatients, and (4) have been receiving any OAC for at least 3 months before enrollment. Additionally, patients must provide informed consent. Exclusion criteria are those who have been treated with OAC for a brief period and are not on treatment anymore (ie, less than 3 months), patients with serious comorbidities (ie, Charlson Comorbidity Index, CCI >4), patients who have suspended OAC for surgery in the last 3 months, and those with cognitive impairment (assessed using a 6-item screener <4). Furthermore, a core set of sociodemographic and clinical variables will be collected to comprehensively describe the study sample.

### Measurements for Phase 2

The study will collect data on sociodemographic and clinical variables to comprehensively understand the participants. Sociodemographic variables will include age, sex (male or female), marital status, educational level, occupation status (employed or unemployed), socioeconomic status (income exemption—yes or no), and the country of the participants. Regarding clinical variables, the study will record the duration of OAC treatment, the type of OAC used (direct and indirect OAC), and the clinical condition that led to the prescription of OAC. For patients treated with vitamin K antagonists, the study will assess the time in therapeutic range (%) over the last 3 months to determine the effectiveness of treatment. Additionally, the occurrence of thromboembolic or hemorrhagic complications during OAC treatment within the last 3 months will be documented for both direct and indirect OAC users. In addition to the sociodemographic and clinical variables previously outlined, our study will also collect data on the number and types of other medications that participants are taking concurrently with their OAC. This inclusion acknowledges polypharmacy as a critical factor in the management and outcomes of patients with NVAF.

A total of 2 scoring systems, the CHA_2_DS_2_-VASc score [26] and the HAS-BLED (Hypertension, Abnormal liver/renal function, Stroke, Bleeding history or predisposition, Labile international normalized ratio, Elderly, Drugs/alcohol concomitantly) bleeding score [27] will be used to assess the risk factors associated with stroke and bleeding, respectively. The CHA_2_DS_2_-VASc score will help identify patients with a higher risk of stroke, where scores greater than 5 indicate a risk higher than 6.7%. On the other hand, the HAS-BLED bleeding score will be used to assess the risk of bleeding, with scores equal to or higher than 3 indicating a high risk of bleeding. By capturing these variables, the study aims to provide a comprehensive and detailed description of the participants in the research, enabling a thorough analysis of SCSE in OAC management.

### Data Analysis

The relevant number of factors to be retained in EFA data analysis will be done on the parameters of scree-test, parallel analysis, and factor rotation. More specifically, in the parallel analysis, if the eigenvalue of the original data’s factor is greater than the average of the eigenvalues of the parallel factor, that factor is retained. Likewise, the item retention will be assessed using factor loadings evaluations, where items with loadings >.40 will be retained. The structural model derived from EFA has to be used for both language groups in the CFA data analysis. The goodness of each model fit will be assessed based on the indexes of root-mean-square error of approximation (RMSEA; <.01) “excellent fit;” (<.05) “good fit;” (<.08) “mediocre fit;” comparative fit index (CFI) and Tucker-Lewis Index (TLI; >.90) and (>.95) [17,18]; SRMR (<.08) [19]; and chi-square test [25]. Furthermore, the multivariate normality of each model will be checked with the Mardia test, supposing that the multivariate skewness and kurtosis are significant. In the case of normality violation, a robust maximum likelihood estimator will be used.

After estimating the baseline model of scale for each language group, we will perform the Multi-Group Confirmatory Factor Analysis (MGCFA) to assess the cross-cultural validity. In other words, we will assess if the configural, metric, and scalar structure of SCSE-OAM is equivalent across 2 different language groups (English vs the Italian language). Achieving multi-group equivalence is pivotal to generating meaningful cross-group comparisons. Testing the measurement invariance means following a series of iterative analytical steps that bring from the largest model (where each language group has its parameters) to the more restricted one (where all the parameters are equal across the language group). This process stops when the model comparison is significant (ie, the large model fits the data significantly better than the more restricted one). A chi-square difference test will be performed to compare each model with the previous one to check whether a stronger invariance assumption holds. Data analysis will be performed in MPlus (Muthén & Muthén; version 8.1).

Clinical variables (ie, time in therapeutic range and absence of hemorrhagic and thromboembolic complications) will be used to estimate the cutoff points of adequate versus inadequate patients’ SCSE and assess criterion validity, which is the degree to which the score of the SCSE-OAM is an adequate reflection of good anticoagulation control. Sensitivity and specificity analyses will be performed under the receiver operator characteristic curve by using time in the therapeutic range and absence of hemorrhagic and thromboembolic complications as dichotomic outcomes (if the distribution of the outcomes will allow researchers to perform this analysis).

### Phase 3

The third phase of this research protocol focuses on evaluating the reliability and internal consistency of the SCSE-OAM over time. This phase, which is anticipated to end by December 2025, aims to ensure the stability of the developed scale. Two main criteria will be used for this assessment—internal consistency and reliability.

For internal consistency, the degree of interrelatedness among the items of the SCSE-OAM will be evaluated using Cronbach α. This index will be calculated for each unidimensional subscale, as well as for the overall scale. A Cronbach α value equal to or greater than 0.70 will be considered acceptable, indicating a strong internal consistency.

In assessing reliability, a test-retest study design will be used to determine the stability of the SCSE-OAM over time. After a 2-week interval, the second group of patients randomly selected from the previous one (sample B for CFA) will be asked to resubmit the SCSE-OAM. The minimum sample size for this test-retest reliability study will be set at 16 patients, with a power of 80%, a minimally acceptable reliability of 0.60, an expected reliability of 0.90, and α level of 0.05, considering a potential dropout rate of 10%. In addition to the scale responses, relevant clinical variables, such as the number of complications and any changes in the treatment regimen, will be collected to assess patients’ stability over time. The intraclass correlation coefficients with a 95% CI will be calculated using a 2-way random-effects model to evaluate the scale’s stability. This model enables us to assess the consistency of the SCSE-OAM when rated by different raters with characteristics similar to the selected raters in this study. By conducting this reliability phase, the research aims to validate the SCSE-OAM as a reliable and consistent tool for measuring SCSE in the context of OAC management.

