The patients’ eligibility criteria will be adult outpatients (18 years of age or older) with ongoing treatment with OAC at the time of the investigation, with a primary clinical indication for long-term OAC for NVAF, treated for at least 3 months, and who are willing to participate in the study. Instead, patients with cognitive decline (ie, Six Item Screener Test with lower than 4 points) will be excluded. Likewise, a convenience sample of 10 voluntary professionals from all relevant disciplines (ie, physician, nurse, and pharmacist) with documented clinical experiences in OAC for at least 1 year will be involved. Sociodemographic and professional variables will be considered to provide a sample description. Finally, an open-ended question will be included to assess the comprehensive and comprehensibility criteria. More specifically, participants will be asked to evaluate whether the items together comprehensively cover the construct of interest and if the population of interest clearly understands the items and response options to evaluate the face validity. The responses will be systematically analyzed, coded, and compared through a qualitative content analysis approach. Data collection will be done through an e-survey.

Following the achievement of content and face validity, 3 forms of validity will be tested—structural, cross-cultural, and criterion validity. As per the structural validity, we will assess the dimensionality of the construct to be measured (ie, SCSE) by factor analysis. However, no clear hypotheses about the underlying dimensions of the construct in the OAC population are available. Therefore, a 2-fold cross-validation will be performed for each language group, using explorative factor analysis (EFA) to explore relationships between observed variables and underlying factors and identify the most plausible psychometric structure and confirmatory factor analysis (CFA) to confirm the most plausible structure derived from EFA. More specifically, the overall sample for each language group will be randomly resampled to generate a subsample A for performing EFA (roughly 50% of the original sample) and subsample B for performing a CFA using the most plausible psychometric structure derived from EFA (using the second 50% of the original sample).

### Sample Size for Phase 2

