In the field of factor analysis, the sample size estimation for allowing researchers to perform factor analysis properly is based on a rule of thumb supported by the Monte Carlo simulation study of enrolling 10 patients per item and per language group [25]. As a result, the final required sample size will be based on the version of the SCSE-OAM derived from the content validity phase because it depends on the number of items encompassed in the scale. Considering previous similar research in patients with heart failure, 10 items were developed for measuring SCSE for adults with heart failure. We hypothesized a similar number of items. In this case, 100 patients per language group will be necessary for EFA and subsequently for CFA.

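### Letting Mardia's test choose between ordinary and robust ML adds modestly to false rejection of a correct factor model when item skew is mild to moderate

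*Protocol article*

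**What the plan says.** In the protocol article, Data Analysis, the normality check is worded: "the multivariate normality of each model will be checked with the Mardia test, supposing that the multivariate skewness and kurtosis are significant". The consequence follows: "In the case of normality violation, a robust maximum likelihood estimator will be used". No other estimator is named, so ordinary ML is the implied choice when the check raises no objection. No significance level is given. The text does not settle whether one or both Mardia statistics must be significant.

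Fit of each model is assessed by RMSEA, CFI, TLI, SRMR and the chi-square test. For measurement invariance between the languages, "A chi-square difference test will be performed to compare each model with the previous one".

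On sample size, the article applies a rule of "enrolling 10 patients per item and per language group" to a scale assumed to have about ten items, and concludes that "100 patients per language group will be necessary for EFA and subsequently for CFA". Under Phase 2: Validation, each language group is split at random and the CFA is run "using the second 50% of the original sample".

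**The concern.** The rule treats failure to reject normality as evidence of normality. Questionnaire ratings are discrete, so exact multivariate normality is false before any data arrive. The test mainly shows whether the sample is large enough to reveal it. When the test misses real skew, the analyst falls back on the ordinary ML chi-square, which is too large for skewed items, and a correct factor structure is rejected more often than it should be. The chi-square is one of the listed fit criteria and also drives the invariance steps.

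Because the either/both condition and the significance level are open, the estimator could also be settled after the data are seen.

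**Working it through.** **1. The plan's own figure.** 10 items × 10 patients per item = 100 per language group, as stated. Half of that for the CFA is 100 × 0.5 = 50. If 100 is meant for each of the two analyses, the group is 200 and the CFA half is 100. Both sizes were examined.

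**2. Assumptions.** The article gives no response format, expected skew, loadings or significance level, so these are assumed.
- Ten five-point items with item skew −0.5, −0.8, −1.1 or −1.9.
- A correct one-factor model with loadings of 0.5 or 0.7.
- Mardia skewness (small-sample corrected) and kurtosis, each tested at 0.05.
- Model degrees of freedom: 10 × 11 / 2 − 20 = 35.
- 4,000 replicates per setting. The Monte Carlo standard error is √(0.15 × 0.85 / 4000) ≈ 0.6 points, and larger in subsets.
- The robust statistic is the ML chi-square divided by a scaling factor (Satorra-Bentler). The nominal rejection rate is 5%.

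**3. Formula.** The rule differs from always-robust only where the switch is not triggered. Its cost is therefore

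cost = P(not triggered) × (ML rejection − robust rejection, both in those samples).

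**4. If either statistic triggers the switch**

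| n | skew | loading | missed | ML rejects, missed samples | robust, same samples | cost (points) |
|---|---|---|---|---|---|---|
| 50 | −0.5 | 0.5 | 76% | 16.4% | 12.8% | 0.76 × 3.6 = 2.7 |
| 50 | −0.5 | 0.7 | 64% | 23.9% | 15.3% | 0.64 × 8.6 = 5.5 |
| 50 | −0.8 | 0.5 | 34% | 22.5% | 16.4% | 0.34 × 6.1 = 2.1 |
| 50 | −0.8 | 0.7 | 14% | 27.9% | 17.9% | 0.14 × 10.0 = 1.4 |
| 100 | −0.5 | 0.5 | 54% | 11.5% | 8.5% | 0.54 × 3.0 = 1.6 |
| 100 | −0.5 | 0.7 | 35% | 14.2% | 9.4% | 0.35 × 4.8 = 1.7 |

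At n = 100 and skew −0.8, only 2% (loading 0.5) or 0.6% (0.7) is missed. At skew −1.1 the misses are 1.5% or 0.4% at n = 50 and none at n = 100.

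**5. Whole procedure: false rejection of the correct model, with the difference from always-robust in brackets**

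| n | skew | loading | always robust | switch if either | switch only if both |
|---|---|---|---|---|---|
| 50 | −0.5 | 0.5 | 13.3% | 16.0% (+2.7) | 17.1% (+3.8) |
| 50 | −0.5 | 0.7 | 14.6% | 20.1% (+5.5) | 24.2% (+9.6) |
| 50 | −0.8 | 0.5 | 13.8% | 15.9% (+2.1) | 22.0% (+8.2) |
| 50 | −0.8 | 0.7 | 15.2% | 16.7% (+1.5) | 26.8% (+11.6) |
| 50 | −1.1 | 0.5 | 14.2% | 14.2% (0.0) | 20.3% (+6.1) |
| 50 | −1.1 | 0.7 | 15.8% | 15.9% (+0.1) | 18.7% (+2.9) |
| 100 | −0.5 | 0.5 | 8.0% | 9.6% (+1.6) | 11.4% (+3.4) |
| 100 | −0.5 | 0.7 | 8.7% | 10.4% (+1.7) | 15.1% (+6.4) |
| 100 | −0.8 | 0.5 | 7.7% | 7.8% (+0.1) | 12.4% (+4.7) |
| 100 | −0.8 | 0.7 | 8.5% | 8.5% (0.0) | 10.8% (+2.3) |

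At skew −1.9 ordinary ML rejects 48–85%, but Mardia's test detects that skew essentially every time, so the rule and always-robust coincide.

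**6. Baseline with exactly normal data.** ML rejects 14.1% and 15.1% at n = 50 (loadings 0.5 and 0.7) and 8.4% at n = 100. Robust ML rejects 14.3% and 15.2%, and 8.6% and 8.9%.

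The share of the excess over 5% that always-robust would leave in place is (always robust − 5) / (rule − 5). At n = 50 and loading 0.7:
- Skew −0.5, either: (14.6 − 5) / (20.1 − 5) = 64%.
- Skew −0.8, both: (15.2 − 5) / (26.8 − 5) = 47%.

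These are the lowest shares in the n = 50 rows under each reading. The highest are 100% (either; skew −1.1, loading 0.5) and 79% (both; skew −1.1, loading 0.7).

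**7. Second simulation (loadings 0.65, skew about −0.7).** At n = 50 the rule rejects 18% (either) or 23% (both), against 16% always-robust. At n = 100 it rejects 11% or 16%, against 11%. A Yuan-Bentler-type correction gave almost no gain at n = 50.

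**The case against.** The strongest reply is that the rule fails mainly where it matters least. Severe skew damages ordinary ML badly, and there the test fires. Mild skew is missed, but ML is then only moderately affected. This stands, and it is why the point is minor.

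Several stronger readings are tempting, but the documents and the calculations do not support them.

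- **A reader might infer that the Mardia rule causes the over-rejection.** It adds to it. ML already rejects about 13–15% at n = 50 with normal data, and naming robust ML would not restore 5%.
- **A reader might infer that both statistics must be significant.** The phrase is awkward and sets no clear two-part rule. It could even mean that the authors expect non-normality and see robust ML as the likely route. The larger figures apply only under the both reading.
- **A reader might infer that the CFA has 50 patients per language.** The sample-size sentence can also mean 100 for each analysis.
- **A reader might infer that the two baseline models become incomparable if the languages receive different estimators.** Under the either rule at n = 50, with equal skew and independent samples, different estimators would arise with probability 2p(1 − p): 2 × 0.64 × 0.36 = 46% at a miss rate of 64%. But the plan sets each baseline model against fixed thresholds and makes the cross-language comparison through nested multi-group models, so little follows.
- **A reader might infer that a correct structure would be discarded.** CFI, TLI and SRMR also count. RMSEA and the chi-square difference tests were not simulated.

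It is also fair to say that discreteness argues at least as much for an estimator designed for ordinal items. That is a legitimate alternative to robust ML.

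**Conclusion.** The point holds in a limited form. The article states a test-then-choose rule, so this is not a detail left to a fuller plan, and the rule is weaker than naming the estimator in advance. For mild to moderate skew its cost in false rejection of a correct model is:

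- either statistic suffices: about 0 to 5.5 points at n = 50, at most about 2 at n = 100;
- both required: about 3 to 12 points at n = 50, up to about 6 at n = 100.

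At n = 50, most of the excess over 5% under the either reading, and roughly half or more under the both reading, would remain under robust ML. With strong skew the rule does no harm. All sizes rest on the assumed five-point format, loadings, 0.05 level and mean-scaled correction. The change is desirable rather than essential.

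**What to change.** Replace the conditional sentence with a fixed choice: robust ML with a mean-scaled (Satorra-Bentler type) chi-square for every CFA and multi-group CFA model in both languages, and the correspondingly scaled chi-square difference for nested models. Report Mardia's coefficients as description only. Name the type of correction, because a Yuan-Bentler-type statistic brought almost no gain at n = 50. State the CFA sample size per language explicitly, since the small-sample excess depends on it and this change does not remove it.

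The cost is about one sentence and no new data. The downside is a slightly noisier test if the data were truly normal: 0.1 to 0.2 points more rejection at n = 50 in the simulation above, with about 0 to 3 points as a cautious range.

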**Methods:**

Using a multiphase, mixed methods observational study design, we first conceptualize the SCSE-OAC through literature reviews, patient focus groups, and expert consensus. The scale’s content validity will be evaluated through patient and expert reviews, while its construct validity is assessed using exploratory and confirmatory factor analyses, ensuring cross-cultural applicability. Criterion validity will be examined through correlations with clinical outcomes. Reliability will be tested via internal consistency and test-retest reliability measures. The study will involve adult outpatients with NVAF on OAC treatment for a minimum of 3 months, using both e-surveys and paper forms for data collection.

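### Criterion validity and the SCSE cutoff rest on a ROC of dichotomised TTR, available only in vitamin K antagonist users, and of 3-month complications, in a sample sized only for factor analysis

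*Protocol article*

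**What the plan says.** In the Protocol article, Methods, Data Analysis, the clinical variables serve two purposes. They "will be used to estimate the cutoff points of adequate versus inadequate" SCSE, and they are the standard for criterion validity, defined there as how well the score reflects good control of anticoagulation. The method is sensitivity and specificity under a ROC curve, "by using time in the therapeutic range and absence of hemorrhagic and thromboembolic complications as dichotomic outcomes", subject to a proviso: "if the distribution of the outcomes will allow researchers to perform this analysis".

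Other sections decide who contributes to that analysis:

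- Eligibility Criteria for Phase 2 admits patients who "have been receiving any OAC for at least 3 months before enrollment".
- Measurements for Phase 2 restricts TTR: "For patients treated with vitamin K antagonists, the study will assess the time in therapeutic range (%) over the last 3 months".
- The same section records complications "within the last 3 months will be documented for both direct and indirect OAC users".
- Sample Size for Phase 2 uses 10 patients per item per language group, a factor-analysis rule.
- The random split into two halves is assigned only to exploratory and confirmatory factor analysis.

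The Abstract describes a different approach: "Criterion validity will be examined through correlations with clinical outcomes". The Results section also anticipates correlations with clinical outcomes. Methods does not specify any such correlation.

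**The concern.** The scale is meant for all patients with NVAF on any OAC, but the two reference outcomes do not cover them equally. TTR measures anticoagulation control and exists for one drug class. Complications exist for everyone, but over a window of only 3 months, in outpatients from whom those with serious comorbidity have been excluded. A direct-OAC user is therefore classified without any measure of the quality the section names as its criterion.

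Three statistical problems follow. The sample was not sized for a ROC analysis, so the AUC and cutoff may be imprecise. TTR is a percentage, and splitting it in two throws away information. A cutoff picked to perform well in a dataset will appear more accurate there than elsewhere, and the article describes no other data in which to judge it.

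The cutoff would label patients as inadequate, and the Results section expects the scale to pick out patients at risk of poor adherence for targeted education. An unstable or flattering cutoff would carry over into that use.

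**Working it through.** **Inputs from the article.** 10 patients per item × 10 hypothesised items = 100 per language group, which reproduces the stated figure. Two language groups give 200 in total if each 100 is divided between the two factor analyses, or 400 if each analysis needs its own 100. No event count or precision target is stated for the ROC.

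**Inputs assumed.** The article gives none of these: 3-month complication rate 1–10%; vitamin K antagonist share 10–50%; 40% of those users with poor TTR; true AUC 0.70; correlation of SCSE with TTR 0.30; 60 vitamin K antagonist users (30% of 200).

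**Step 1: precision of the AUC (Hanley–McNeil).** With A = 0.70, u = A/(2−A) = 0.538 and v = 2A²/(1+A) = 0.576,

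SE² = [A(1−A) + (n₁−1)(u−A²) + (n₀−1)(v−A²)] / (n₁n₀).

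For 10 events and 190 non-events: (0.21 + 9×0.0485 + 189×0.0865)/1900 = 0.00894, so SE = 0.095 and the 95% half-width is 1.96×0.095 = 0.19.

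| Complication rate | Events in 200 | Half-width | Events in 400 | Half-width |
|---|---|---|---|---|
| 1% | 2 | 0.41 | 4 | 0.29 |
| 2% | 4 | 0.29 | 8 | 0.21 |
| 3% | 6 | 0.24 | 12 | 0.17 |
| 5% | 10 | 0.19 | 20 | 0.13 |
| 10% | 20 | 0.13 | 40 | 0.09 |

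With 2 events the upper limit would be 0.70 + 0.41 = 1.11, beyond the possible range. The normal approximation has failed there, and that entry means only that the AUC is uninformative. The exact binomial probability of fewer than 10 events in 200 is 99% at a 2% rate and 46% at 5%.

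The same formula for TTR, with 40% poor:

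| Vitamin K antagonist share | Users in 200 | Half-width | Users in 400 | Half-width |
|---|---|---|---|---|
| 10% | 20 | 0.25 | 40 | 0.17 |
| 20% | 40 | 0.17 | 80 | 0.12 |
| 30% | 60 | 0.14 | 120 | 0.10 |
| 50% | 100 | 0.11 | 200 | 0.08 |

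**Step 2: information lost by splitting TTR.** Under bivariate normality, a median split multiplies the correlation by φ(0)/0.5 = 0.399/0.5 = 0.798. The square is 0.637, so about 36% of the information goes. A correlation of 0.30 becomes 0.798 × 0.30 = 0.239. Power by Fisher's z with n = 60:

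- r = 0.30: atanh = 0.310; × √57 = 2.34; 2.34 − 1.96 = 0.38; power 65%.
- r = 0.239: atanh = 0.244; × √57 = 1.84; 1.84 − 1.96 = −0.12; power 45%.

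The median is the kindest split under this model. At 40/60 the factor is 0.386/√(0.4×0.6) = 0.386/0.490 = 0.79.

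**Step 3: optimism of a data-chosen cutoff.** Two normal score distributions with AUC 0.70 differ by d = √2 × Φ⁻¹(0.70) = 0.742. The best attainable Youden index is 2Φ(d/2) − 1 = 2Φ(0.371) − 1 = 0.29. In 4,000 simulated datasets per case, the Youden-optimal cutoff was chosen and evaluated in the same data:

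| Cases / non-cases | Mean apparent Youden | True Youden of chosen cutoffs | SD of cutoff (score SDs) |
|---|---|---|---|
| 4 / 196 | 0.50 | 0.24 | 0.69 |
| 10 / 190 | 0.42 | 0.26 | 0.53 |
| 20 / 380 | 0.38 | 0.26 | 0.44 |
| 24 / 36 (TTR, 60 users) | 0.39 | 0.26 | 0.47 |
| 80 / 120 (TTR, 200 users) | 0.34 | 0.27 | 0.34 |

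The optimism shrinks with sample size but remains in the largest case shown.

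**The case against.** **The proviso.** The authors foresaw sparse outcomes and made the ROC conditional on the outcome distribution. That stands in part: a ROC on one or two events is unlikely to be run. But the proviso decides only whether the ROC is run. It does not give direct-OAC users a measure of control, restore the information lost by splitting TTR, or correct a cutoff that is kept.

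**Detail left to a fuller document.** The TTR threshold, the rule for choosing the cutoff and any bootstrap correction may be in a full protocol or SAP that is not shown. Their absence is not the point here. Dichotomising TTR, using a reference limited to one drug class, and drawing the cutoff partly from 3-month complications are choices the article states.

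**Stronger readings that do not hold.**

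- A reader might infer that the cutoff is undefined for direct-OAC users. It is not: complications are recorded "within the last 3 months will be documented for both direct and indirect OAC users", so one can be computed.
- A reader might infer that complications are rare. The short window and the comorbidity exclusion make that plausible, but the article gives no rate.
- A reader might infer that nothing is left if the ROC is dropped. The Abstract names correlations; Methods does not say which ones or in whom.
- A reader might infer that TTR and complications are offered as a gold standard for self-efficacy. The article claims only that the score should reflect anticoagulation control.

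**Size.** Imprecision is not certain. With 400 patients, a 10% complication rate gives a half-width of 0.09 and a 50% vitamin K antagonist share gives 0.08.

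**Conclusion.** The concern holds in a limited form. From the text alone: TTR covers only vitamin K antagonist users; the direct-OAC cutoff would rest on complications alone; the sample is sized only for factor analysis; and the correlations promised in the Abstract are not specified in Methods.

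The loss from splitting TTR and the optimism of a cutoff judged where it was chosen do not depend on the complication rate. Their sizes do depend on assumptions: a factor of about 0.80 on the correlation (normality, median split), and an apparent Youden of about 0.39 against an attainable 0.29 (AUC 0.70, 60 users, 40% poor TTR, no correction).

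Imprecision is likely but conditional. At an assumed complication rate of 1–5%, the AUC half-width is roughly 0.13–0.41 across the two readings of the total, and the largest value is only indicative. The plan should be amended on this point. The factor-analytic validation is unaffected.

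**What to change.** In Data Analysis:

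1. Make the main criterion-validity analysis the Spearman correlation (or a regression) of SCSE score with continuous TTR in vitamin K antagonist users, with a 95% CI. This also supplies the analysis the Abstract promises.
2. Report complications by OAC type as a descriptive contrast in SCSE score.
3. If a ROC cutoff is still produced, label it exploratory, name the OAC group it was estimated in, and report bootstrap optimism-corrected sensitivity, specificity and AUC with CIs.

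The cost is some revised wording and a few lines of code, with no new data. The downside is that reported accuracy will be lower and no TTR-based cutoff is claimed for direct-OAC users.
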